##### 2.7.2.2 Fear-Avoidance Beliefs Questionnaire (FABQ)

The FABQ comprises two independent subscales and includes a total of 16 self-report items. The FABQ-Phys, which contains 5 items and has a total score range of 0 to 24, is intended to assess fear-avoidance beliefs related to general physical activities. The FABQ-Work, comprising 11 items with a total score range of 0 to 42, is employed to evaluate fear-avoidance beliefs associated with occupational activities. A higher score indicates a higher level of fear-avoidance beliefs (28). The MCID values for FABQ-Work and FABQ-Phys are 7 points and 4 points, respectively (29).

##### 2.7.2.3 36-Item Short Form Health Survey (SF-36)

This questionnaire consists of 36 questions that evaluate the impact of pain on patients’ daily health status across eight dimensions, and has been widely applied in medical research. The overall score spans a range from 0 up to 100, where lower numerical values are indicative of a diminished quality of life (30). Generally, an increase of 30% in the SF-36 score will be considered clinically significant (31).

##### 2.7.2.4 Global Perceived Effect (GPE)

This outcome measure employs a single-item self-assessment tool in which participants indicate their perceived changes in clinical status. The scoring range of this scale extends from −5 to +5. A score of + 5 is assigned when patients report complete resolution of pain symptoms following treatment, whereas a score of 0 indicates no perceived change in pain symptoms, and a score of −5 reflects significant exacerbation of pain symptoms after treatment (32). The MCID has been defined as 1.7 points for chronic LBP (33).

##### 2.7.2.5 fNIRS

Pain is closely associated with the functional connectivity of relevant cerebral cortical regions. fNIRS is an emerging optical imaging technique that reflects cortical activation patterns associated with neuronal activity by detecting concentration changes in oxygenated hemoglobin (HbO_2_) within localized cerebral regions (34). fNIRS examinations will be conducted in a quiet room with subdued lighting. Data acquisition will be performed using a 48-channel near-infrared optical imaging system (NirScan-6000A, HuiChuang Medical Equipment Co., Ltd., Danyang, China). This system operates at two wavelengths (730 nm, and 850 nm) with a sampling rate of 11 Hz. It comprises 15 light source optodes and 16 photodetector probes, with an optode-to-detector distance of 3 cm. Light sources and detectors will be symmetrically distributed over the bilateral dorsolateral prefrontal cortex (DLPFC), primary motor cortex (M1), primary somatosensory cortex (S1), premotor cortex (PMC), and supplementary motor area (SMA) in accordance with the international 10-20 standard electrode placement system. Acquired data will be analyzed using the NirSpark software.

### 2.8 Safety evaluation and adverse events (AEs)

Continuous safety monitoring of participants will be required during each intervention session throughout the trial. All AEs that occur during the intervention or follow-up periods will be systematically documented in the case report forms (CRF), along with a careful assessment of their potential association with moxibustion therapy. Potential risks associated with moxibustion include skin burns, blistering, pruritus, dizziness, and other post-moxibustion discomforts. In the event of an AE, regardless of its perceived relationship to the study, qualified medical professionals will be required to provide immediate symptomatic treatment and appropriate interventions. Researchers will complete detailed documentation in the CRF regarding the AE’s onset time, specific manifestations, severity grading, therapeutic measures implemented, and clinical outcomes. Safety monitoring will continue until resolution or stabilization of the participant’s condition. All AEs will be reported to the trial’s principal investigator (PI) and the institutional ethics committee for review, followed by subsequent evaluation of the participant’s eligibility for continued trial participation. Compensation procedures will be activated for study-related serious adverse events (SAEs) in accordance with regulatory requirements and institutional policies.

### 2.9 Data management and quality control

The data collected by professional physicians will be stored in a dedicated electronic database, and the participants’ identifying information will be concealed using numerical codes. Each participating research center will be responsible for monitoring data quality. To maintain procedural consistency across study centers, quarterly investigator meetings are planned to address emerging trial-related issues and facilitate ongoing communication with all research personnel. To enhance participant compliance, researchers will provide timely reminders via telephone for scheduled visits and assessments. For subjects who withdraw from the clinical trial or follow-up, detailed documentation of reasons and outcomes will be systematically recorded.

### 2.10 Sample size calculation

The sample size calculation was performed using G*Power software (version 3.1.9.7; University of Düsseldorf, Germany). The calculation was based on a prior clinical trial evaluating acupuncture for CNLBP, which also used the NRS as the primary outcome measure (35). According to the reported data from that study, the post-treatment mean ± standard deviation (SD) was 2.96 ± 3.44 for the treatment group (*n* = 29) and 2.00 ± 2.79 for the control group (*n* = 28), yielding an effect size of 0.3 (Cohen’s d), suggesting a small intervention effect. Considering subjective feedback from CNLBP patients who had previously received moxibustion therapy regarding its perceived efficacy, we estimated a potential effect size of 0.5 (moderate effect) for moxibustion treatment. With α set at 0.05, power (1-β) at 0.80, and these parameters entered into G*Power, the calculation indicated a required sample size of 64 participants per group. Accounting for an expected 15% dropout rate during the trial, the total sample size was adjusted to 150 participants (75 per group).

### 2.11 Statistical analysis

To minimize potential biases arising from manual intervention, the statistical analyses for this study will be conducted independently by two blinded statisticians using SPSS (version 25), both of whom will be unaware of the group assignments and treatment details. Data analysis will adhere to the intention-to-treat principle. Participants who complete the baseline assessment of the primary outcome and receive at least one session of moxibustion or sham moxibustion treatment will be included in the ITT analysis. Continuous variables will be presented as mean ± standard deviation (SD) or median (P25-P75), with statistical comparisons performed using Student’s *t*-test or non-parametric Mann-Whitney U test as appropriate. Categorical variables will be described as frequencies and percentages, with between-group differences analyzed via χ^2^ test or Fisher’s exact test. It should be noted that all baseline comparisons serve solely to verify inter-group balance after randomization, and their results will not be used to adjust the primary analysis model. For repeatedly measured outcome variables, a random-intercept mixed-effects model (MMRM) will be employed. Specifically, the model will include observed values at each scheduled assessment timepoint (weeks 4, 8, and 16) as dependent variables, with baseline values incorporated as fixed-effect covariates. Treatment group (moxibustion vs. sham moxibustion), timepoint (weeks 4, 8, and 16), and their interaction will be modeled as fixed-effect categorical variables. Additionally, individual subject intercepts will be included as random effects. Between-group comparisons at each timepoint will be estimated through least squares mean differences derived from treatment-by-time interaction terms, with corresponding *P*-values and 95% confidence intervals (CI) reported. All statistical tests will be two-sided, and a *P*-value < 0.05 will be considered statistically significant.

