#### 2.3.3 Suspension criteria

(1) Patients who refuse to continue participation for personal reasons during the trial;

(2) Occurrence of serious adverse events (SAEs) directly attributable to the intervention, including skin burns, syncope, or other life-threatening complications;

(3) Participants demonstrating non-compliance with the study protocol, such as unscheduled treatment modifications or concurrent use of prohibited therapies.

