### 2.4 Randomization

The study will employ a permuted block randomization method (with block size set to 4) stratified by research center for sequential allocation of participants. The randomization sequence will be generated by a statistician independent of the study team using SAS software (version 9.4; SAS Institute Inc., Cary, NC, USA). Research personnel will have no access to the randomization sequence. Randomization numbers will be sealed in sequentially numbered opaque envelopes and stored in a double-locked cabinet. Following completion of baseline assessments and submission of informed consent forms, envelopes will be opened in sequential order of enrollment to reveal group assignments. The allocation sequence will remain concealed such that the next participant’s assignment cannot be predicted in advance.

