### 2.5 Blinding

Throughout the trial, the subjects will remain blinded to their group assignments. Specifically, each subject will be assigned to a separate treatment room to prevent participant-to-participant communication. Due to the unique characteristics of moxibustion therapy, it is difficult to implement blinding among the treating physicians. However, the data collectors, outcome assessors, and statisticians will be blinded to the details of treatment allocation and group assignments throughout the trial. Moreover, they will not be permitted to share any research-related information with each other. This approach will enhance the reliability of the study results. Unblinding will occur only in the event of serious adverse events or after study completion and final data analysis.

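### The set called ITT is defined by receiving at least one session, so it is a modified (treated) set; the exclusion is probably small but should be corrected or renamed

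*Protocol article*

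**What the plan says.** Section 2.11 (Statistical analysis) states: "Data analysis will adhere to the intention-to-treat principle". The next sentence sets two conditions for membership. The participant must have completed the baseline assessment of the primary outcome, and must "receive at least one session of moxibustion or sham moxibustion treatment will be included in the ITT analysis". The article describes no other analysis set.

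Section 2.4 (Randomization) gives the order of events. Once baseline assessment and consent are complete, "envelopes will be opened in sequential order of enrollment to reveal group assignments".

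Section 2.5 (Blinding) says that "the subjects will remain blinded to their group assignments" and that "the data collectors, outcome assessors, and statisticians will be blinded to the details of treatment allocation and group assignments throughout the trial". Of those who deliver treatment it says that "it is difficult to implement blinding among the treating physicians".

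**The concern.** Intention-to-treat means that everyone randomised is analysed in the arm assigned, whatever treatment followed. The rule in section 2.11 removes anyone randomised who has no session. Having a session is decided after allocation, so the two sentences of section 2.11 disagree.

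Leaving out people who never start is fairly safe when nobody who can influence the start knows the arm. That defence is only partly available here, because the practitioners are unblinded. If staff who know the allocation affect whether a first session takes place, membership of the primary set could depend on both arm and prognosis. The week-8 NRS comparison would then no longer rest wholly on randomisation, and a report calling it ITT would misdescribe it.

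**Working it through.** **1. The plan's own figure.** Section 2.10 gives "With α set at 0.05, power (1-β) at 0.80" with d = 0.5; section 2.11 makes tests two-sided. A two-sample t-test calculation (noncentral t) gives 63.77, so 64 per group, with power 0.801 at 64. This agrees with the article. For 15% dropout, 128/0.85 = 150.6, against the stated 150 (75 per group). The sample size is not in dispute; it supplies the 75 per arm and the 0.5 SD target used below.

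**2. Which condition excludes anyone.**
- Baseline NRS completed: under section 2.4 this precedes the envelope, so it should exclude nobody randomised.
- At least one session received: this can only be met after allocation, so it alone makes the set a modified one.

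**3. Who could know the arm before session 1.** Sections 2.6.1 and 2.6.2 use different set-ups: the burning end 3–5 cm from the acupoint in one arm, and 8–10 cm with an insulating membrane in the other. Whoever prepares the first session must know the arm. Section 2.4 does not name the person who opens the envelope or state word for word that this precedes treatment. Practitioner knowledge before session 1 is therefore inferred from the sequence, though no other order is workable.

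**4. Size of the possible bias.** The number of never-treated participants is not given, so k and g are assumptions. Let k of 75 be excluded from one arm and none from the other, and let their mean lie g SD from that arm's full mean. The mean of those remaining moves by

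bias = k·g / (75 − k) SD.

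Type I error is approximated from the normal distribution with no true effect and SE = √(1/(75 − k) + 1/75).

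| k | g | Bias (SD) | Share of 0.5 SD | Type I error |
|---|---|---|---|---|
| 1 | 0.5 | 0.5/74 = 0.007 | 1.4% | 0.050 |
| 1 | 1.0 | 1/74 = 0.014 | 2.7% | 0.051 |
| 2 | 0.5 | 1/73 = 0.014 | 2.7% | 0.051 |
| 2 | 1.0 | 2/73 = 0.027 | 5.5% | 0.053 |
| 4 | 0.5 | 2/71 = 0.028 | 5.6% | 0.053 |
| 4 | 1.0 | 4/71 = 0.056 | 11.3% | 0.063 |
| 8 | 0.5 | 4/67 = 0.060 | 11.9% | 0.065 |
| 8 | 1.0 | 8/67 = 0.119 | 23.9% | 0.110 |

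For scale in NRS points, the SDs quoted in section 2.10 pool to √((28 × 3.44² + 27 × 2.79²)/55) = 3.14. The 2-exclusion, 1 SD case is then 0.027 × 3.14 = 0.09 points, and the 8-exclusion, 1 SD case is 0.119 × 3.14 = 0.37 points.

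Equal exclusions of similar patients from both arms would largely cancel. The direction depends on which arm loses patients and whether they would have done better or worse, so it cannot be known in advance.

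**5. Effect of analysing everyone as randomised.** Suppose k of 75 in the moxibustion arm never start and have sham-level outcomes. The expected effect is d = 0.5 × (1 − k/75).

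| k | d | Power at 64 evaluable per group |
|---|---|---|
| 0 | 0.500 | 0.80 |
| 1 | 0.493 | 0.79 |
| 2 | 0.487 | 0.78 |
| 4 | 0.473 | 0.76 |
| 8 | 0.447 | 0.71 |

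**The case against.** **Blinding.** Participants do not know their arm, so their own decision not to attend a first session should depend little on it. Data collectors, assessors and statisticians are blinded too. What remains is staff who know the allocation keeping a consented, randomised participant from even one of 24 sessions (three a week for 8 weeks). Nothing in the article suggests that this is expected. This stands, and it is the main reason to expect a small effect.

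**Likely numbers.** The larger table rows need a one-sided loss of several patients and a full 1 SD difference. The 15% in section 2.10 is dropout over the whole trial; 8 of 75 never starting in one arm (10.7%) would be about 70% of that. This also stands: the rows for 1 or 2 exclusions are the more natural reference.

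**Redefinition alone may change little.** The model in section 2.11 uses values observed at weeks 4, 8 and 16. A never-treated participant with none of these adds nothing, whatever the set is called. This is correct, and the change is therefore only useful with outcome collection.

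**A stronger reading the documents do not support.** Section 2.3.3 lists among its suspension criteria "Participants demonstrating non-compliance with the study protocol, such as unscheduled treatment modifications or concurrent use of prohibited therapies". A reader might infer that suspension thins the primary set further, or that week-8 data will be lost unequally, with more losses under sham. Anyone suspended after one session still meets the section 2.11 condition and stays in the set. The article does not say that suspended participants stop assessments, and it gives no basis for expecting more of them in one arm. How off-treatment follow-up is organised is detail that a condensed article may leave to the full protocol.

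None of this removes the contradiction: the set is defined explicitly, and the definition is not intention-to-treat.

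**Conclusion.** The point holds. Section 2.11 claims intention-to-treat and defines a treated set, and no other section repairs this. Because practitioners are unblinded and probably know the arm before session 1, the exclusion cannot be assumed independent of arm.

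The consequence is probably small. On the assumptions shown, one or two one-sided exclusions shift the comparison by under 6% of the planned effect and leave type I error at 0.050 to 0.053. Only with about 8 exclusions from one arm and a 1 SD difference does the shift reach about 24%, with type I error near 0.11. It would go too far to say that the randomised comparison is broken: the article gives no never-treated count, and blinding of participants and assessors closes most routes.

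This should be corrected before analysis, but does not by itself threaten the trial's conclusion. It is best settled while follow-up is possible, since NRS ratings never collected cannot be recovered.

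**What to change.** - Define the primary analysis set as all randomised participants, in their assigned arm, whatever treatment they received.
- Seek NRS at weeks 4, 8 and 16 from participants who never start treatment, unless they withdraw consent for data, and use those values in the mixed model.
- Keep the current set as a supportive analysis named modified ITT.
- Report by arm the number randomised who had no session, so that readers can judge the exclusion directly.

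The cost is a change of wording and a few extra NRS ratings; the total stays at 150. The estimate may be slightly diluted: d of about 0.49 to 0.47 if 1 to 4 of 75 never start moxibustion and have sham-level outcomes. If outcomes cannot be obtained from those who never start, the least change is to rename the set modified ITT and withdraw the claim of intention-to-treat.

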### 2.7 Outcome measures

The assessment of outcomes encompasses the following domains: low back pain intensity, somatic dysfunction, pain-related fear and avoidance behaviors, health status, and cerebral cortex activation characteristics. Assessments will be performed at baseline, mid-intervention (week 4), post-intervention (week 8), and follow-up (week 16). It is worth mentioning that participants will be required to rate the overall efficacy of the received intervention using the Global Perceived Effect (GPE), at week 8 (post-intervention). Additionally, functional near-infrared spectroscopy (fNIRS) will be employed by the researchers to assess cerebral cortex activation characteristics in each group at baseline and week 8 (end of intervention).

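### GPE, measured once at week 8, falls by exclusion to an unadjusted t-test or Mann-Whitney test with no rule for choosing and no promised difference with CI: a minor, cheaply mended weakness in one secondary outcome

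*Protocol article*

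**What the plan says.** Section 2.11 (Statistical analysis) describes two routes for continuous data.

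- **General rule.** Continuous variables are summarised as mean and SD or as median and quartiles, and compared by Student's t-test or the "non-parametric Mann-Whitney U test as appropriate". No covariate is mentioned, and nothing says what makes either test appropriate.
- **Repeated outcomes.** "For repeatedly measured outcome variables, a random-intercept mixed-effects model (MMRM) will be employed". It covers weeks 4, 8 and 16, "with baseline values incorporated as fixed-effect covariates", and yields least squares mean differences with P-values and 95% CIs at each timepoint.

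GPE is not named in section 2.11. Section 2.7 and Table 1 place it at week 8 only. NRS, ODI, FABQ and SF-36 are each taken at four visits, and fNIRS at baseline and week 8, so GPE is the only outcome measured once. Section 2.7.2.4 describes a single self-rated item on perceived change in pain: "The scoring range of this scale extends from −5 to +5". It adds: "The MCID has been defined as 1.7 points for chronic LBP".

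Section 2.11 also makes a baseline assessment of the primary outcome (NRS) a condition of entry to the ITT set.

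**The concern.** A model over weeks 4, 8 and 16 that adjusts for the outcome's own baseline cannot take an outcome with a single value and no baseline. GPE is therefore left with the general rule, and two weaknesses follow.

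1. **Reporting.** The two tests under the general rule answer different questions. The t-test concerns a difference in mean points, while the Mann-Whitney test compares ranks. With no criterion for choosing, the form of the GPE result is open until the data are seen, and section 2.11 has two statisticians analysing independently with nothing to make them take the same branch. Intervals for between-group differences are promised only in the mixed-model text.
2. **Efficiency.** GPE rates change in pain, and pain at baseline is recorded for everyone in the analysis set. If baseline NRS predicts week-8 GPE, an unadjusted comparison has a larger standard error than the collected data require.

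The stake is the precision and readability of one secondary outcome.

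**Working it through.** **1. The plan's own figure.** Section 2.10 gives 64 per group for NRS at a standardised difference of 0.5, α = 0.05 and power 0.80; section 2.11 makes tests two-sided. The normal approximation gives 63 per group. The noncentral t calculation gives 63.8, hence 64, with power 0.801. The figure reproduces. It concerns NRS; the document gives no SD, effect size or power for GPE.

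**2. Which method reaches GPE.**

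| Outcome | Visits (Table 1) | Method under section 2.11 |
|---|---|---|
| NRS, ODI, FABQ, SF-36 | 0, 4, 8, 16 weeks | baseline-adjusted mixed model |
| GPE | 8 weeks | not named; only the t-test or Mann-Whitney rule is left |

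**3. Inputs for the size of the gain.**

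- Evaluable participants: 64 per group, 128 in total (section 2.10, before dropout).
- Correlation r between baseline NRS and week-8 GPE: not in the document. Assumed range for |r|: 0 to 0.4.
- Standardised GPE difference for the power column: 0.5, an assumption borrowed from the NRS calculation.

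**4. Formulas.** Adjusting for a covariate with correlation r multiplies the variance of the group difference by 1 − r².

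- Standard error ratio = √(1 − r²)
- Equivalent extra completers = 128/(1 − r²) − 128
- Power: noncentral t at 0.5/√(1 − r²), 64 per group, two-sided 0.05

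**5. Results.**

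| Assumed \|r\| | 1 − r² | SE ratio | SE falls by | Equivalent extra completers | Power |
|---|---|---|---|---|---|
| 0 | 1.00 | 1.000 | 0% | 0 | 0.801 |
| 0.1 | 0.99 | 0.995 | 0.5% | 1.3 | 0.805 |
| 0.2 | 0.96 | 0.980 | 2.0% | 5.3 | 0.817 |
| 0.3 | 0.91 | 0.954 | 4.6% | 12.7 | 0.837 |
| 0.4 | 0.84 | 0.917 | 8.3% | 24.4 | 0.865 |

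These figures ignore the small cost of estimating the extra coefficients. Baseline NRS takes one degree of freedom and three centres take two, so the residual falls from 128 − 2 = 126 to 123. At |r| = 0.1 that cost could absorb much of the gain.

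**6. What each branch delivers.** The t-test branch yields a mean difference in GPE points, for which a CI is easily given although none is promised. The Mann-Whitney branch yields a rank-based P-value. The group medians and quartiles that section 2.11 provides for are on the GPE scale, but they are descriptive and give no interval for a difference.

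**The case against.** The strongest reply is that nothing here is wrong. An unadjusted comparison of two randomised groups is valid, and its standard error already allows for chance imbalance in baseline pain. That stands. A reader might infer that the GPE contrast is biased, or that imbalance enters it unaccounted for; the document does not support this.

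A second reply is that GPE is never assigned a method, and that the t-test sentence may be meant partly for baseline tables, since the text soon turns to baseline comparisons. It is true that the assignment is by exclusion. But the sentence is not confined to baseline, and no other route is given for a single-visit score. A separate analysis plan may refine this; the comment here is on the rule as stated.

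Third, the usual case for adjusting an outcome for its own baseline does not carry over, because GPE has none and is already a rating of change. The NRS ≥ 3 entry criterion (section 2.3.1) may also limit the correlation. This stands: a reader might infer that precision is certainly lost, but without a value for r the document cannot show that.

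Fourth, a reader might infer that the GPE result could not be compared with its 1.7-point MCID. That goes too far. The difficulty arises only in the Mann-Whitney branch, and section 2.7.2.4 does not say whether 1.7 points is a within-patient or a between-group threshold, or that the group difference will be judged by it.

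One further reply fails. Section 2.11 says that baseline test results will not be used to adjust the primary model. That rules out data-driven adjustment of the primary analysis, not a prespecified covariate for a secondary outcome.

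**Conclusion.** The point holds as a minor improvement. On the text, GPE is left by exclusion to an unadjusted test, with an open choice between a difference in means and a rank comparison, and with no interval promised. The reporting weakness needs no assumption beyond that reading. The efficiency weakness does: the standard error would fall by 0% to 8.3% over an assumed |r| of 0 to 0.4, and by nothing if baseline NRS and GPE are unrelated. The power figures also borrow an effect size that the protocol sets only for NRS. The planned comparison is valid, the primary result is unaffected, and no conclusion is shown to change.

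**What to change.** Add one sentence to section 2.11: week-8 GPE will be analysed by a linear model with treatment group, baseline NRS and centre, and reported as an adjusted mean difference with 95% CI, with the Mann-Whitney test as a sensitivity check. Centre belongs in the model because randomisation is stratified by it (section 2.4). Cite the 1.7-point MCID as context only, unless the protocol states that it applies to between-group differences.

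The change needs no new data, and no one in the ITT set is lost for want of baseline NRS. It costs three degrees of freedom and means fitting a linear model to an 11-step bounded scale, which is why the rank test is worth keeping as a check.

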**FIGURE 1 F1:**
[figure not shown]
Trial flow diagram.

**TABLE 1 T1:** Trial schedule.

	Study period			
	Inclusion	Treatment		Follow-up
Assessment	Baseline	Second	Third	Fourth
Measure point (after inclusion)	0 week	4 weeks	8 weeks	16 weeks
Inclusion criteria	✓			
Exclusion criteria	✓			
Informed consent	✓			
Randomization and allocation	✓			
Intervention		1–8 week		
NRS	✓	✓	✓	✓
ODI	✓	✓	✓	✓
FABQ	✓	✓	✓	✓
SF-36	✓	✓	✓	✓
GPE			✓	
fNIRS	✓		✓	
Adverse events	Any time during the intervention and follow-up			

✓, required; NRS, Numerical Rating Scale; ODI, Oswestry Disability Index; FABQ, Fear Avoidance Beliefs Questionnaire; SF-36, 36-Item Short Form Health Survey; GPE, Global Perceived Effect.

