#### 2.7.1 Primary outcome

##### 2.7.1.1 Numeric Rating Scale (NRS)

This instrument serves as a standardized tool for assessing lumbar pain intensity, utilizing a numerical rating system spanning from 0 (indicating complete absence of pain) to 10 (representing the maximum tolerable pain threshold) (11). For patients with chronic LBP, a 2-point difference on the NRS was defined as the minimal clinically important difference (MCID) (25). The NRS score at week 8 will be regarded as the primary outcome measure.

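### The model labelled MMRM is specified with only a random intercept, which as usually fitted imposes compound symmetry and can misstate the week-8 standard error

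*Protocol article*

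**What the plan says.** Section 2.11 of the protocol article states that for outcomes measured repeatedly "a random-intercept mixed-effects model (MMRM) will be employed". It then sets the model out. On the outcome side, "the model will include observed values at each scheduled assessment timepoint (weeks 4, 8, and 16) as dependent variables". Baseline, group, visit and the group-by-visit interaction are fixed effects. For the within-subject part, "individual subject intercepts will be included as random effects". No residual covariance, robust standard error or alternative structure is named.

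The same section takes the treatment effect from this model: "Between-group comparisons at each timepoint will be estimated through least squares mean differences derived from treatment-by-time interaction terms". Section 2.7.1.1 fixes the primary endpoint: "The NRS score at week 8 will be regarded as the primary outcome measure". Table 1 shows the NRS collected at baseline and at weeks 4, 8 and 16, so this model yields the primary contrast.

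**The concern.** The label and the specification point to different covariance models. An MMRM models the within-subject covariance directly, most often as unstructured. A random intercept with independent, equal-variance residuals gives every visit the variance s_b² + s_e² and every pair of visits the same correlation.

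The design gives reason to doubt that constraint. Two of the modelled visits fall in the treatment period and the third comes 8 weeks after it ends, so the spread of scores may well differ between visits. The plan does not need the assumption, yet the standard error of the primary contrast rests on it. When week-8 values are missing, so does the estimate, because the model fills the gap through its implied regression of week 8 on week 4. Section 2.11 also has two statisticians analyse the data independently. One could follow the label and the other the specification, and so fit different models.

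**Working it through.** **The plan's own figure.** Section 2.10 works from "With α set at 0.05, power (1-β) at 0.80" and an effect size of 0.5. A two-sample t-test calculation gives 63.77, so 64 per group, as stated. This figure does not depend on the covariance structure, and the point below leaves it unchanged.

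**Standard error with complete data.** The random-intercept model estimates one variance, the mean of the three visit variances, and uses it at every visit. For week 8:

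- r = model SE / true SE = sqrt(mean visit variance / week-8 variance)
- true type I error = 2 × (1 − Φ(1.96 r))
- approximate power at d = 0.5 with 64 per arm = Φ(0.5 / sqrt(2/64) − 1.96 r) = Φ(2.828 − 1.96 r)

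The document gives no visit SDs, so every SD below is an assumption. They stand for residual SDs after baseline adjustment.

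| SDs at weeks 4/8/16 | Mean variance | Week-8 variance | r | Week-8 type I error |
|---|---|---|---|---|
| 2.0/2.0/2.0 | 4.00 | 4.00 | 1.000 | 5.0% |
| 1.8/2.1/2.3 | 4.31 | 4.41 | 0.989 | 5.3% |
| 2.0/2.5/3.0 | 6.42 | 6.25 | 1.013 | 4.7% |
| 2.5/2.2/2.0 | 5.03 | 4.84 | 1.019 | 4.6% |
| 1.4/2.2/2.3 | 4.03 | 4.84 | 0.912 | 7.4% |
| 2.0/2.7/2.5 | 5.85 | 7.29 | 0.896 | 7.9% |
| 1.5/2.5/2.5 | 4.92 | 6.25 | 0.887 | 8.2% |
| 1.8/2.0/2.8 | 5.03 | 4.00 | 1.121 | 2.8% |

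In the last row the SE is too large, and power falls from Φ(0.868) = 0.81 to Φ(0.631) = 0.74. Where the SDs change in roughly equal steps (rows 2 to 4), week 8 is near nominal because it is the middle visit. The error then moves to the outer visits: with 2.0/2.5/3.0 the type I error is 1.3% at week 4 (r = 1.267) and 9.8% at week 16 (r = 0.844).

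Simulated complete-data trials (75 per arm, 600 runs per pattern, REML, the plan's fixed effects) agree on the SE. The mean random-intercept SE divided by the mean unstructured SE was 0.329/0.360 = 0.914 for 1.4/2.2/2.3 and 0.367/0.328 = 1.119 for 1.8/2.0/2.8. The formula gives 0.912 and 1.121. Simulated type I error is noisier, with a Monte Carlo SE of sqrt(0.05 × 0.95 / 600) = 0.9 percentage points.

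**Bias with dropout.** Take SDs 2.0/2.7/2.5 and correlations 0.75 (weeks 4 and 8), 0.65 (8 and 16) and 0.45 (4 and 16), again assumed.

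- True slope of week 8 on week 4: 0.75 × 2.7 / 2.0 = 1.01.
- Compound-symmetry slope: mean covariance / mean variance = [(4.05 + 4.39 + 2.25) / 3] / 5.85 = 0.61.

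The random-intercept model therefore pulls a dropout's implied week-8 score too far towards the arm mean. Large-sample week-8 bias under missing at random, with dropout after week 4 driven by the week-4 score:

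- Same direction in both arms, 20% sham and 10% verum, SDs as above: roughly 0.05 to 0.13 points, depending on how strongly pain drives dropout.
- Same direction, same dropout rule in both arms (12% to 15% lost), other SD patterns: about 0.03 points at most.
- Opposite directions by arm, 16% to 19% lost: 0.06 (equal SDs, decaying correlation) to 0.25 (1.4/2.2/2.3).
- Compound symmetry true: about 0.00.
- Unstructured covariance: within 0.005 points of zero in every pattern run.

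**The case against.** The strongest reply is that the constraint is inferred. Section 2.11 never states the residual covariance, a random intercept can sit beside a heterogeneous residual matrix, and a journal article commonly leaves estimation details to a fuller document. MMRM does not by itself mean unstructured either. This stands in part. The absence of degrees-of-freedom or convergence rules is no fault here, and compound symmetry follows only under the usual reading. But the article does not leave the within-subject model open: it chooses a random intercept and adds nothing to it.

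The second reply is about size, and it stands. No visit SDs or correlations are given. The larger week-8 errors need a week-8 variance that stands apart from the average of the three visits.

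A reader might go further than the document supports in four ways:

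- That the week-8 confidence interval and p-value are wrong whenever variances differ. They are not: rows 2 to 4 of the table have unequal variances and stay between 4.6% and 5.3%.
- That unequal spacing or falling correlation distorts the week-8 SE. With complete data only the variances enter r; correlation matters only through missing values.
- That pain-related dropout biases the primary estimate substantially. Same-direction dropout at 20% versus 10% gives roughly 0.05 to 0.13 points, small beside the 2-point MCID in section 2.7.1.1. Larger values come from opposite-direction dropout, which nothing in the article predicts.
- That week 16 is a key secondary contrast. The article ranks no secondary outcome or timepoint; week 16 is simply one of the modelled visits.

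**Conclusion.** The point holds as a correctable weakness in stated text. The mismatch between label and specification is certain; its numerical effect is not. Assuming independent, equal-variance residuals, week-8 type I error lies between about 3% and 8% over the assumed SD patterns, and near 5% if variance is equal or changes steadily. In the steady case weeks 4 and 16 carry the error. Dropout can add a slight bias at week 8 if it depends on week-4 pain differently by arm. That bias vanishes with complete data or if compound symmetry is true, and is about zero with an unstructured covariance. Nothing here shows that the primary result will be wrong. It shows that its validity depends on an assumption that the trial has no need to make.

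**What to change.** In section 2.11, replace the random intercept with an unstructured within-subject covariance across weeks 4, 8 and 16, fitted by REML. Prespecify a heterogeneous-variance structure, such as heterogeneous Toeplitz or heterogeneous first-order autoregressive, in case it does not converge. The fixed effects can stay as written. If the random intercept is what the sponsor intends, the MMRM label should go and compound symmetry should be justified.

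The cost is wording. The covariance has six parameters (three variances and three covariances) instead of two, so four more, which is negligible with 150 participants. Sample size, visits and data collection do not change.
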